## **1. IDENTIFICATION OF THE PROTOCOL**

- **EUDRACT number:**
- **Promoter protocol code:** BRLUCM2020-1
- **Version/Date:** 10 December 2020

## **2. EC TITLE**

Evaluation of the effectiveness of a Training Program in the Cultivation of Compassion in medical students of the Complutense University of Madrid.

## **4. RELEVANT ASPECTS ABOUT THE FINANCING OF THE STUDY:**

This study is the continuation of a Teaching Innovation Project (PID) of the UCM that began last year (PID nº 334, 2019-2020), and that has been granted again this year (PID nº 139, 2020-2021). This year's project does not have its own funding.

The Nirakara Institute, associated with the Extraordinary Chair of "Mindfulness and Cognitive Sciences" of the Complutense University of Madrid, will provide the software required for online assessment (i.e., Qualtrics)

The Lilly Foundation will donate a book to each study participant as a final thank you for their participation in the trial.

## **6. REFERENCE CEIC**

Not applicable

## **8. JUSTIFICATION AND RELEVANCE OF THE STUDY**

### **8.1 Current situation**

#### **8.1.1 Compassion and medicine**

Compassion, the foundation of medical ethics (Fotaki, 2015), suffers a crisis in health today (Trzeciak, 2017). Offering empathetic and compassionate care benefits:

(i) patients by improving clinical outcomes (Kim, 2004; Rakel, 2009; Hojat, 2011; Attar 2012; Del Canale, 2012; Steinhausen, 2014; Trzeciak, 2017; Moss, 2019) -- Patients are open to treatment when they feel heard by their doctors -- (Zolnierrek, 2009), decrease depression and improve their quality of life (Burns 1992; Zachariae, 2003; Neumann, 2007) or reduce anxiety in cancer patients (Fogarty, 1999); (i) health professionals, reducing burnout and improving their well-being after repeated contact with the patient's suffering and; iii) to the health system, reducing economic costs (Epstein, 2005). Despite this evidence, doctors often miss opportunities to be compassionate, limiting their performance to biomedical exploration and explanation (Epstein, 2007).

#### **8.1.2. Discomfort in health professionals**

Facing suffering without being able to act according to one's beliefs and values due to hierarchical or institutional pressures can lead to burnout in professionals, increase medical errors (Kelm, 2014), obtain suboptimal results in the evolution of patients (Shanafelt, 2002; McHugh, 2011) or decrease empathy and increase dehumanization (Dzeng, 2016). Compassion fatigue, a type of burnout among caregivers of those who suffer (Figley, 1995), is prevalent in medicine (Van Mol, 2015; Sprang, 2007), reaching epidemic levels among licensed and trainee physicians (West, 2016).

### **8.1.3. Training in compassion and medicine: effects**

Empathy and compassion can be trained and improved (Stepien, 2006; Hojat, 2009a; Goetz, 2010; Kelm, 2014). Although related, empathy and compassion stimulate different brain centers; empathy those of pain (Lamm, 2011 ) and compassion those of reward (Lamm, 2011; Klimecki, 2014). This last aspect acquires relevance in the medical profession, and helps to explain why the practice of compassion constitutes a protective factor against empathic distress, preventing compassion fatigue. Recent studies manifest brain plasticity and suggest that compassion training activates brain regions associated with positive conditions (Klimecki, 2013; Weng, 2013).

### **8.1.4. Compassion in medical studies**

Some studies demonstrate a decrease in empathy and compassion during medical school and residency (Hojat, 2004; Bellini, 2005; Stepien, 2006; Neumann, 2011), especially in the transition to contact with patients (Hojat, 2009b; Neumann, 2011; Wilson, 2012). Other data indicate that medical students start the career in better mental health conditions than individuals of the same age enrolled in other careers, deducing that medical studies contribute to the deterioration of the mental health of students (Brazeau, 2014).

However, compassion is not a primary goal of career teaching even though the compassion of health professionals can be improved with training (Hojat, 2004; Stepien, 2006; Kelm, 2014).

Institutions such as the American Association of Medical Colleges or the American Medical Association are underscoring the importance of compassionate patient care (AAMC; Kelm, 2014). This belief is supported by recent publications (Patel, 2019) and studies conducted with medical students in which it is concluded that: i) compassion training can be an effective and attractive option to reduce burnout and, at the same time, promote the well-being of students and improve their interactions with patients; and ii) teachers should consider offering these skills to students as it appears to reduce empathic erosion suffered by students more directly than stress management training in isolation (Weingartner, 2019).

#### **8.1.5. Previous experience of the research group in teaching the CCT to medical students.**

The results found by us in the Teaching Innovation Project of the UCM for the 2019-20 academic year (PID nº 334, precedent of the present study collected in PID nº 139 2020-21) coincide with findings from the literature (Weingartner, 2019). In this preliminary study, our students significantly increased: i) their sense of shared humanity; (ii) all parameters related to mindfulness; (iii) the ability to remain in the face of discomfort without distress and; iv) self-friendliness (unpublished data, collected in the memory of PID nº 339 2019-20). In summary, the skills learned helped them reduce the stress associated with their personal and academic lives, and reinforce their personal and patient interactions.

#### **8.2. What the test will bring**

- Benefits for the health of the participant, derived from developing greater self-compassion, happiness, joy, empathy and compassion towards the other, as well as greater resilience that helps them reduce the levels of stress and anxiety during the race, the exercise of their profession and their personal life.
- Favor the development of courage to approach, understand and relate to suffering (own and others) without having to move away from it (i.e. prevent empathic distress), and the growth of motivation to alleviate suffering.
- Participants, students and future medical professionals, trained in compassion, enjoying greater personal well-being, will have a greater ability to provide compassionate care to their patients, which will result in providing them with more effective care, better therapeutic outcomes and a better coexistence of these with their disease, with the positive impact that this will have on families.
- Establish the bases in the Faculty of Medicine of the UCM to provide society with more compassionate doctors and therefore, favor the growth of a more humane health, in line with the tendency to promote patient-centered health systems
- Contribute to the Faculty of Medicine of the UCM being an example of humanization of teaching.

#### **8.3. Information on the CST™ programme**

The CCT™ protocol, developed at Stanford University by contemplative scholars, clinical psychologists and researchers, and currently sponsored by the Institute of Compassion. CCT™ is a secular program that integrates traditional contemplative practices with contemporary psychology and scientific research on compassion. The CCT™ is an 8-week blended course that combines a 2.30-hour face-to-face session each week with internships during the week. The goal of the CCT™ in medicine is to develop a compassionate mind and heart that provides skills for self-care and fosters compassionate interaction with patients.

Compassion, defined as sensitivity to one's own suffering and that of others, along with a deep commitment to seek to alleviate it, is a basic capacity for care inherent in the human being that allows one to respond to suffering with understanding, patience and kindness, rather than with fear and repulsion. Compassion can be trained (Stepien, 2006; Hojat, 2009a, Goetz, 2010; Kelm, 2014), and through his practice, improve compassion for oneself and extend it to those people who are difficult for us. The CCT™ program is based on developing a genuine compassion that arises from recognizing that the suffering of others is similar to our own and that like us, others also wish to be free from such suffering. From this statement, emerges the empathic concern that sensitizes us to the pain of others. Far from implying pity (it places the one who experiences it in a situation of superiority), condescension, permissiveness, or absence of limits, compassion is related to the courage to face suffering and remain in the face of it, and with the motivation to do something to diminish it.

#### **8.4. Hypothesis**

1. The standardized Compassion Cultivation Training (CCT) program will produce an improvement in emotional well-being and a reduction in psychological distress (stress, anxiety, depression) and burnout of post-program medical students compared to a control group on the waiting list.
2. Such changes shall be maintained over time two and six months after the end of the programme.
3. The above changes will be driven by increases in compassion for oneself, compassion for others, attention to the present moment, and emotional regulation skills.
4. The skills developed in the program will be a protective factor for the management of stress and psychological distress caused by the COVID-19 pandemic.

#### **9. DESIGN**

A randomized, controlled, unicentric trial will be conducted with a control group on the waiting list (parallel groups). A 1:1 randomization will be performed (using the relevant function in Excell), with a single-blind masking. The simple blind is guaranteed by the division of weights in the research team, so that the person in charge of the evaluation and analysis of data does not participate and is blind to the process of randomization and the formation of the groups (RP). The IP of the project (BR) will be in charge of summoning the participants and assigning the groups.

##### **9.1 Study design**

We will perform an analysis of the participants' responses to an online protocol made up of different psychometrically validated psychological measures, which will be completed by the participants at different times (Fig. 1). These questionnaires will be used as quantitative indicators of the psychological changes experienced by the participants in the main outcomes and targets of the CCT® program.

[figure not shown]

**Figure 1. CONSORT diagram**

In a **first phase**, participants will be randomized into the two study groups (Fig. 1): experimental group (i.e., CCT program) or control group on waiting list. Such randomization shall be carried out after baseline assessment to avoid the occurrence of biases produced by expectations of participation in the CCT® program.

In a **second phase**, 2 months after the end of the first CST programme (CST-1), in February 2021, participants on the waiting list will be offered the possibility of participating in the CST programme by becoming the CCT-2® group.

People who voluntarily want to participate in the research will commit to carry out a pre-program® evaluation, a brief inter-sessional evaluations during the program, an evaluation at the end of the program and an evaluation at 2 and 6 months after the end of the program. During the first phase of the study, the waiting list group (control group) will undergo the same evaluations and at the same times as the CCT-1 group.

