### **11.2 Program Details**

The CCT® program consists of 6 steps that are developed in eight weeks. Specifically:

*Week 1. Settlement and approach*

Development of mindfulness, settling the mind on the present experience with acceptance and without judgment through exercises aimed at focusing attention on the breath by loving, with kindness, attention back whenever it is distracted.

*Week 2. Compassion as a natural capacity*

Learn to recognize the physical and psychic signs associated with compassion through dialogue and guided exercises.

*Week 3. Self-pity*

It presents the idea that the cultivation of self-compassion is the basis for developing compassionate behavior towards others. Training in the practice of self-compassionate dialogue, self-acceptance and growth of these skills in difficult situations.

*Week 4. Self-love*

Learn to cultivate warmth, appreciation, joy and gratitude for oneself.

*Week 5. Shared humanity*

Recognition of shared humanity (seeing the other "just as I am") and interdependence as the foundation of compassion toward others.

*Week 6. Compassion*

From shared humanity and interdependence, cultivate compassion for all beings, including difficult ones.

*Week 7. Active compassion*

Aimed at developing inner stability to welcome the suffering of others and offer one's own happiness.

*Week 8. Integrated Compassion Cultivation Practice*

Bring together the elements of the previous steps into a compassionate meditation practice that can be followed as a daily practice

These six steps will be developed through:

- 8 weekly meetings of 2h online duration (due to COVID-19) consisting of relational exercises, meditations and dialogues on pedagogy and science related to the theme of the week. The online meetings will be held through the Zoom platform.
- Guided meditations recorded in audios of 20-30 min duration to be carried out daily (formal practices).
- Informal practices in everyday life

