### **13.2. Estimation of possible loss**

In order to minimize the sample loss throughout the study, we have adopted several measures aimed at maintaining motivation and reinforcing the participation of the participants: the members of the control group will sign an agreement to carry out the relevant evaluations to formalize the reservation of their place in the second promotion of the course. Once the study is completed, participants will be rewarded with an ECTS credit of free configuration (approved by the UCM Studies Commission on November 12, 2020) and object of academic recognition for the degree in medicine. In addition, participants who complete all evaluations of the study will receive a gift book on the theme of the program. For all the above, we expect a sample loss of less than 5%.

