#### **14. STATISTICAL ANALYSIS**

Following the CONSORT recommendations, Intention-To-Treat Analysis will be performed to handle lost data. A diagnosis of the randomness pattern of the loss will begin using Little's MCAR test. The baseline differences between completers (i.e., per-protocol) and missing will also be analyzed to determine if there are any variables in the dataset that predict data loss. Depending on the loss pattern, multiple imputations will be made or by means of Maximum Likelihood algorithms. Finally, sensitivity analyses will be performed comparing the per-protocol data with the imputed ones to determine if the imputation has generated biased estimates. As indicated in the previous section, the criterion of attendance at 75% of the sessions of the program will be used as an indicator of "minimal exposure to treatment".

Student's t-tests and chi-square tests will be used to analyze differences between groups at baseline. The main analysis will be a mixed ANOVA with two factors: independent measures group factor (experimental vs control) and repeated measures time factor (pre, post, follow-up 2 and 6 months). ANCOVAs will also be performed using baseline as a covariate in analyses and repeated measure ANOVAs to assess the maintenance of changes over time. The analysis of variance will be complemented by mediating and moderating analyses to study the mechanisms of change of the program. A significance

level of alpha 0.05 will be defined in bilateral contrasts. Statistical analyses will be carried out using SPSS (v. 25) and R (v. 3.6.1) software.

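### Six months stays in the main experimental-versus-control ANOVA although controls are offered the programme four months earlier, so that level has no untreated comparator

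*Protocol*

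**What the plan says.** **Crossover.** The text under Figure 1 (Section 9.1) sets a second phase, "2 months after the end of the first CST programme (CST-1), in February 2021", in which "participants on the waiting list will be offered the possibility of participating in the CST programme" and so form a second-course group. Section 13.2 has controls sign an agreement "to formalize the reservation of their place in the second promotion of the course". Uptake is therefore planned, but it is optional and no figure is given.

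**Course length.** Section 11.2: "The CCT ® program consists of 6 steps that are developed in eight weeks".

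**Assessments.** Participants commit to "an evaluation at 2 and 6 months after the end of the program". For controls, parallel assessment is tied to the first phase: "During the first phase of the study, the waiting list group (control group) will undergo the same evaluations and at the same times" as the first-course group.

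**Analysis.** Section 14 makes the main analysis a mixed ANOVA with a between-subject factor (experimental against control) and a "repeated measures time factor (pre, post, follow-up 2 and 6 months"). It adds ANCOVAs with baseline as covariate, and separate repeated-measures ANOVAs for maintenance.

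**Hypotheses.** In Section 8.4, hypothesis 1 compares post-programme status with the waiting list. Hypothesis 2 follows: "Such changes shall be maintained over time two and six months after the end of the programme". Secondary objective 1 (Section 10) repeats the maintenance aim without naming a comparator.

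**The concern.** The main model needs the control arm to mean the same thing at all four times. It does so at baseline, post-programme and 2 months. By 6 months, controls who took up the offer have been trained. No text at hand removes the 6-month level from the between-arm factor, relabels the controls there, or limits the randomised comparison to 2 months.

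Two misreadings follow. A durable benefit can look lost at 6 months because the controls have caught up. A significant omnibus interaction can arise partly from the controls' own improvement. If every control crosses over and gains equally, a durable effect produces the between-arm pattern (0, d, d, 0). An effect that vanished by 6 months with no crossover produces the same pattern, so the group-by-time test cannot tell them apart.

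**Working it through.** **1. Timeline, counted from the end of the first course**

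- Controls are offered the course at +2 months (text under Figure 1).
- Eight weeks is about 2 months (Section 11.2), so a prompt starter finishes at about 2 + 2 = +4 months.
- The 6-month evaluation is at +6 months, about 2 months after that.

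The protocol gives no start date for the second course, so a prompt start is an assumption. The +2-month offset holds whether February 2021 dates the offer or the end of the first course.

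**2. What the 6-month control cell can contain**

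- Controls assessed at +6 months: largely trained against trained.
- Parallel assessment confined to the first phase: no control value at that time.
- Controls' follow-up counted from the end of their own course: the time levels no longer align between arms.
- Only controls who decline the course kept: randomisation is broken.

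None of these gives a randomised untreated comparator.

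**3. The plan's own figure**

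Section 13.1 gives effect size 0.40, alpha 0.05, power 90% and N = 44. I take 0.40 as Cohen's f, which for two groups is d = 2 × 0.40 = 0.8. The noncentral F for the between-group effect has λ = f²·N·m / (1 + (m − 1)ρ), with 1 and N − 2 df. With m = 4 times and ρ = 0.5 (both assumed):

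λ = 0.16 × 44 × 4 / 2.5 = 11.26; power 0.906. The stated 44 is reproduced.

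With m = 3 (pre, post, 2 months) the same option needs N = 46. With m = 2, the pre-post change that Section 13.1 names, it gives 52; that is a separate matter.

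**4. Effect of uptake u**

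Assumed: true effect 0.8 SD, fully maintained; the same gain in crossed-over controls; 22 per arm; ρ = 0.5 with compound symmetry; two-sided alpha 0.05. The between-arm differences are (0, 0.8, 0.8, δ), with δ = 0.8(1 − u).

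- 6-month contrast: two-sample t, 42 df, noncentrality δ√(22/2).
- Group main effect: λ = (22/2) × 4 × (mean difference)² / 2.5, with 1 and 42 df.
- Interaction: λ = (22/2) × Σ(difference − mean)² / (1 − 0.5), with 3 and 126 df.

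At u = 0: mean 0.60, sum of squares 0.48; λ = 6.34 (group) and 10.56 (interaction).
At u = 1: mean 0.40, sum of squares 0.64; λ = 2.82 (group) and 14.08 (interaction).

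| Uptake | 6-month difference (SD) | Power, 6-month contrast | Power, group main effect | Power, interaction |
|---|---|---|---|---|
| 0% | 0.80 | 74% | 69% | 77% |
| 50% | 0.40 | 25% | 54% | 73% |
| 90% | 0.08 | 6% | 41% | 85% |
| 100% | 0 | 5% | 37% | 89% |

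If crossed-over controls gain only half the effect, full uptake leaves 0.40 SD and 25% power for the 6-month contrast.

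**5. After the fix**

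With three times the differences are (0, 0.8, 0.8) at any uptake. The sum of squares is 0.4267, λ = 11 × 0.4267 / 0.5 = 9.39, and interaction power is 77% with 2 and 84 df.

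**The case against.** The best defence is that little of the trial depends on the 6-month cell. Hypothesis 1 concerns post-programme status, the sample size was set for pre-post change, and baseline-adjusted ANCOVAs at post or 2 months contain no crossover. All of that stands. The defect is confined to the four-level model and to between-arm statements at 6 months.

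Several stronger readings are tempting but not supported:

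- *The maintenance analysis treats controls as untreated at 6 months.* Hypothesis 2 and secondary objective 1 name no comparator at that time, and the repeated-measures ANOVAs can be read as within-arm. That reading is legitimate but uncontrolled, and the protocol does not say which is meant.
- *Untreated control values would be imputed at 6 months.* Section 14 imputes lost data. A value that was never scheduled is not lost, and nothing says it would be filled in.
- *The 2-month comparison is contaminated.* The course is offered then, but no session is placed before the 2-month questionnaire.
- *Crossover always inflates the interaction.* At 50% uptake its power falls from 77% to 73%; it rises only at high uptake.
- *The lack of control for academic calendar or pandemic wave is an error.* It is an inherent limit of a waiting-list design with delayed treatment.

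The four-time group main effect is also a weak yardstick because it averages in baseline. Under the fix its power is only 56% (mean difference 0.533, λ = 11 × 3 × 0.533² / 2 = 4.69).

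Figure 1 is not shown and may list the control assessments, and an analysis plan may exist. Neither would change the fact that Section 14 itself fixes 6 months as a level of the main model.

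**Conclusion.** The point holds for the main ANOVA. The crossover described under Figure 1 and the four-level time factor in Section 14 do not fit together. The 6-month level offers no randomised comparison with an untreated waiting list, and the omnibus test that includes it cannot be read as one.

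The size depends on uptake, which the protocol does not give. Under the assumptions above, the expected 6-month difference runs from 0.80 SD with no uptake to zero with full uptake, and the power of that contrast from 74% to 5%. The interaction test moves between 73% and 89% at the uptakes tabulated, in no single direction. The timeline assumes that controls start promptly when offered the course.

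The pre-post and 2-month comparisons remain sound. The sample size is hardly touched: 46 instead of 44 under the option that reproduces the stated figure.

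**What to change.** - **Section 14:** limit the randomised group-by-time model and the between-arm ANCOVAs to pre, post and 2 months. State that the controls' 2-month evaluation is taken before any session of their own course.
- **Section 14:** report 6 months only as a change within the first-course arm, with a 95% confidence interval, labelled uncontrolled.
- **Sections 8.4 and 10:** reword hypothesis 2 and secondary objective 1 so that between-arm maintenance is claimed at 2 months only, with 6 months descriptive.

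The cost is wording; no new data are needed. The price is a weaker 6-month maintenance claim, which this design cannot support as a randomised comparison in any case.
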